### 2.2. Study Site

The study will take place in the districts of Hoima (intervention district) and Masindi (control district) in the Bunyoro sub-region in western Uganda. ttC will be implemented in the Hoima district, because this district has one of the highest maternal mortality rates in Uganda [14]. Masindi has been selected as the control district because it has a similar profile of maternal, newborn and child health determinants compared to Hoima. Some examples of similarities in key indicators for Hoima [15] and Masindi [16] are the number of females aged 18 years and above who are illiterate (38.4%, and 39.5%, respectively)**,** children aged 0–17 who lost both parents (0.7% and 0.2%), females aged 12–17 who have ever given birth (11.8% and 10.5%), and households located 5 km or more from the nearest health facility (39.5% and 29.5%).

Both Hoima and Masindi have functional VHTs who have received basic training on the roles and responsibilities in the delivery and reporting of community health. They have also received the necessary materials to assist them in their work and the two districts had VHT capacity assessed for their level of functionality before the training. All VHTs [17] in Uganda must undergo a five-day training course, be equipped with a participant’s manual, a household register, cards for counselling purposes and a monthly reporting book before they are fully qualified to provide community health services. Partners who wish to provide additional capacity-building to the VHTs first make sure that the VHTs are trained in the general strategy. However, for the intervention district, additional training has been done to facilitate the implementation of ttC to improve MNCH indicators and deliverables.

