### 2.8. Sample Size

The sample size is calculated using the formula for comparing differences in rates and proportions between two groups and determining the number of subjects per group^n^, using an individual binary for a two-sided significant level α and power 1-β [27]. With an anticipated effect size of 10% [δBinary = (^μ^T − ^μ^C)], α = 0.05 (two-sided), β = 0.2,^ z^1^−α^/2 = desired significance level at 95% (0.05). ^Ζ^1 − β = desired power at 80% (0.842), type of test = two-sided, and absolute risk reduction = 10%.

Since the study focuses on uptake of pregnancy services and essential newborn care, the key participants are pregnant mothers. We, therefore, estimate the pregnancy rate from each area using the 2020 population estimates per district, then turning the pregnancy rate into a percentage proportion. To estimate pregnancy rate, the focus will be on the recommended women of reproductive age within the population. Using the health care planning estimation, it is estimated that 24% of the population are women of reproductive age [28]. An estimation of number of births, abortions and foetal losses was acquired from the actual total 2019 health management and information systems [29] reports for both districts. This provided a 1107-sample size in the two districts. This will be increased by 10% to 1218 participants to cater for a non-response. Therefore, the treatment and control groups will each have 609 mothers at the end of the study.

To determine number of clusters needed (n_cluster) [27,30]: n _cluster = total number of participants in the two groups (/fixed cluster size) which is (^n^Cluster_Binary 2)/m = 1218/60, giving us 20 clusters. In order to have the same number of clusters per arm, the number of clusters will be increased to the nearest upper even number, which is 20 in this study. This means that the sample size contains 1218 pregnant mothers in 20 clusters which is the sub-county by the administrative units of Uganda [31].

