### 2.10. Sampling Procedure

A multi-stage sampling technique will be employed to select study participants. A total of 20 clusters of sub-counties will be selected and included in the study, based on the power calculation. Sub-counties with largest numbers of pregnant mothers registered by the VHTs will be included to ensure that the estimated study sample size is met. This will be used to increase the level of efficiency of sampling and each cluster will be considered as a sampling unit. At the beginning of the study, the team will consult the ttC registers from the VHTs in Hoima and the VHT registers from Masindi to assess the pregnancy registration per sub-county. For each sub-county, six villages will be randomly selected, with each village providing 10 households.

At the household, selection of pregnant mothers to be included in the study will be done systematically. In this probability sampling, participants will be selected from a larger population of pregnant mothers according to a random starting point and a fixed periodic interval. This periodic interval will be determined beforehand as two, which means that assuming the starting point is one as the first serial number on the VHT register, every pregnant mother with an even serial number will be selected to participate in the study, that is, 2, 4, 6, 8, etc. The sampling procedure is presented in Figure 3.

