## 3. Data Management and Analysis

The data from the previous day of the study is entered and cleaned immediately, enabling immediate feedback on any issues to the data collection team. Once the team responsible for the tool returns from the field, brief conversations will be done to ensure that data was not missed at collection level.

Under the guidance of the statistician, a data entry template will be created using the expanded program of immunization info. All data shall be entered using this data entry template. Tools at data collection will be given a unique code. The process of unique coding will include sub-county, parish, village and then household number following the sampling frame. To ensure that each tool has a unique number, data collectors will be assigned numbers to use before heading into the field.

The data after entry is the responsibility of the statistician and the investigators at analysis. This data shall be attached to all publications for the world to have access to. This excludes personal data.

Univariate analysis will be done using SPSS, considering all data that requires a unilateral representation from the study. Baseline data as well as key demographic information from both comparison and implementation sites will be examined.

Several exploratory tests will be done to evaluate the data for dependencies and possible violations of normality and other key assumptions. Bivariate analysis will be used to determine the empirical relationship between study variables. This includes the differences between the implementation and comparison areas. In addition, the relation between the statuses at the baseline and the status of the indicators with a focus on the contribution of ttC will be examined. Next, multivariate analyses will be conducted, adjusting for potential relevant confounders (such as the implementation of a birth plan and a fourth ANC attendance (or more) on clean birthing practices). Depending on preliminary analyses, either fixed or random effects models will be selected for subsequent multivariate analysis, adjusting for the multi-level structure of the data, caused by the clustering of participants within villages.

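### The open fixed-or-random choice, with clustering named only at village level, does not fit a district-assigned design whose stated clusters are 20 sub-counties

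*Protocol article*

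**What the plan says.** Section 3 (Data Management and Analysis) states that, depending on preliminary analyses, "either fixed or random effects models will be selected for subsequent multivariate analysis, adjusting for the multi-level structure of the data". It describes that structure as "caused by the clustering of participants within villages" and names no other level.

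The design sections describe a different hierarchy:

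- Section 2.2 places the study in "the districts of Hoima (intervention district) and Masindi (control district"), so ttC is assigned to one whole district and usual care to the other.
- Section 2.8 concludes that "the sample size contains 1218 pregnant mothers in 20 clusters which is the sub-county by the administrative units of Uganda", with equal numbers of clusters per arm.
- Section 2.10 says that "each cluster will be considered as a sampling unit" and continues: "For each sub-county, six villages will be randomly selected, with each village providing 10 households".

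The note to Table 3 defines the end-term outcome as the comparison between the ttC area and the control area. Section 3 also mentions relating baseline status to the indicators, but states no model that combines baseline and end-term data.

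**The concern.** The analysis sentence and the design sections do not agree on what the clusters are, and one of the two model families may be unable to return the effect the study is meant to estimate.

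Every village and every sub-county lies wholly in one arm. Indicators for either unit therefore already contain all the information that separates Hoima from Masindi. In the other branch, a model with random effects for villages alone treats villages in the same sub-county as independent, so it counts 120 units where the design counts 20. At stake are whether the ttC estimate exists under one branch, and whether its confidence interval and test have their nominal properties under the other. The choice between the branches would be made after looking at the data.

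**Working it through.** **Structure, from the plan's own figures.** 1107 × 1.10 = 1217.7, which gives 1218; 1218/60 = 20.3, taken as 20 sub-counties, hence 10 per arm. Six villages of 10 households give 60 per sub-county, 20 × 6 = 120 villages (60 per arm) and 20 × 60 = 1200 women (600 per arm). The check uses this balanced layout. The plan gives no ICC and no standard error for the ttC effect, so there is no figure of that kind to reproduce.

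**Fixed-effects branch.** Build the end-term design matrix for 20 × 6 × 10 women.

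- 120 village indicators: rank 120. Adding the ttC column makes 121 columns; the rank is still 120.
- 20 sub-county indicators: rank 20. Adding ttC leaves it at 20.
- Pre/post layout in the same villages, with village indicators, a period term and a district-by-period term: 122 columns, rank 122.

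In the end-term comparison, ttC is an exact linear combination of the unit indicators and has no estimable coefficient. In the pre/post layout, the district-by-period term is estimable.

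**Random-effects branch, villages only.** Let s be the sub-county ICC, v the village ICC and e = 1 − s − v, with total variance 1. Per arm:

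- true variance of the arm mean: s/10 + v/60 + e/600
- variance as a village-only model sees it: (s + v)/60 + e/600

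SE ratio = square root of (true / village-only). Actual size of the nominal 5% test = 2 × [1 − Φ(1.96/ratio)]. Assumed v = 0.02; s varied.

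| s | true | village-only | SE ratio | actual test size |
|---|---|---|---|---|
| 0 | 0.001967 | 0.001967 | 1.00 | 5% |
| 0.01 | 0.002950 | 0.002117 | 1.18 | 10% |
| 0.02 | 0.003933 | 0.002267 | 1.32 | 14% |
| 0.03 | 0.004917 | 0.002417 | 1.43 | 17% |
| 0.05 | 0.006883 | 0.002717 | 1.59 | 22% |

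For example, at s = 0.01 the true term is 0.001 + 0.000333 + 0.001617 = 0.002950 and the village-only term is 0.0005 + 0.001617 = 0.002117; √(0.002950/0.002117) = 1.18.

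**Simulation check.** 20,000 runs per setting, a binary outcome at an assumed 60%, v = 0.02, no ttC effect. A t-test on village means rejected in 5.3%, 10.1%, 14.0% and 21.9% of runs at s = 0, 0.01, 0.02 and 0.05. A t-test on sub-county means rejected in 4.9% to 5.2% in the same settings.

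**The case against.** The strongest reply is that section 3 never says village indicators; it says fixed or random effects models. That is right. Village indicators are the natural reading, because the sentence ties the choice to clustering within villages, but they are not stated. Reading fixed effects as having no cluster term at all would contradict the sentence's own claim to adjust for the multi-level structure.

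Second, much of the planned multivariate work is not about the ttC coefficient. The examples in section 3 and the abstract relate woman-level factors, such as antenatal attendance, to outcomes, and the independent variables in Table 4 are woman-level. Unit indicators are legitimate there. They would also work in a pre/post model, and Table 3 does schedule a baseline. This stands, and it limits the point to the end-term ttC comparison; no district-by-period model is stated.

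Third, naming villages does not expressly exclude sub-counties, and an article may leave random-effect levels to a fuller document. Mere silence would not be a finding. Here the text names one level in the analysis and a different one as the cluster in the design.

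Fourth, sub-counties are chosen for their large numbers of registered pregnancies, so they might be viewed as strata rather than sampled clusters. But stratification removes between-stratum variation from a comparison only if both arms occur in each stratum, and no sub-county contains both. The plan itself also calls them clusters and sampling units.

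Finally, a collinear term may be noticed when the model is fitted. It may also not be: software can drop a village column instead and print a ttC coefficient that only contrasts arbitrary reference villages.

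**Conclusion.** The point holds in conditional form. The clustering level named in section 3 conflicts with sections 2.8 and 2.10, and the choice of model family includes an option that, on its natural reading, cannot give the ttC effect in the end-term comparison of the two areas.

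A reader might infer that the plan commits to village fixed effects and so cannot answer its question. The documents do not support that: the wording is not literal, and such effects remain usable for woman-level covariates or a pre/post term. A reader might also infer that the standard errors are certain to be too small. That requires a sub-county ICC above 0, and none is given. For assumed values of 0.01 to 0.05 with a village ICC of 0.02, the understatement is a factor of about 1.18 to 1.59 and the nominal 5% test has a true size of about 10% to 22%; at 0 there is none.

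Nor would a corrected model make the ttC inference fully sound. With one district per arm, any difference between Hoima and Masindi is indistinguishable from ttC, and no random effect at sub-county or village level changes that.

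**What to change.** For the ttC effect, remove the fixed-or-random choice and specify one analysis in advance. Either:

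- a mixed model with ttC as a fixed effect, random intercepts for sub-county and for village within sub-county, and small-sample degrees of freedom (20 sub-counties − 2 arms = 18); or
- an analysis of sub-county summaries, 10 against 10.

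Keep unit fixed effects only for woman-level associations, or for a pre/post model if one is written down with ttC as the district-by-period term. Align the wording of section 3 with sections 2.8 and 2.10. Add a sentence saying that ttC remains confounded with district and that the model does not remove this.

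No new data are needed: section 3 already builds sub-county and village into each record's code. The cost is precision. Relative to a village-only analysis, intervals widen by the factors above, 1.18 to 1.59 under the assumed ICCs. Using t on 18 degrees of freedom (2.101) in place of 1.96 multiplies the width by a further 1.07, giving about 1.27 to 1.71 overall. If the sub-county ICC is near 0, only the 1.07 remains.

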### 3.1. Dissemination of Results

It is envisaged that results from this study will be shared with the community in which it has been carried out focusing on the intervention areas. The Hoima district local government, Ministry of Health and stakeholders. The World Vision Uganda Health and Nutrition Department will be getting updates on the study, and results. The results shall be published in scientific peer reviewed journals with a focus on the midterm review results and the final evaluation results. Overall, good practices will be advocated for even in those communities where the study did not take place. The Ministry of Health will be asked to replicate these findings in other parts of the country. The complete study protocol shall be available plus all data sets during the publication period.

### 3.2. Study Strength and Weaknesses

This study will have several strengths and limitations that shall be considered. The mixed methods design provided unique insights in an understudied research population. The deliberate selection of Masindi District as the control region is aimed at ensuring maximum social-demographic similarities for optimal comparability. The experimental longitudinal design will provide valuable insights, relevant for the community MNCH system policy framework.

The study anticipates to face some recruitment and retention challenges including: women in Uganda having a habit of hiding their pregnancy and therefore delaying to go for ANC and hence missing timely inclusion into the study; and limited father involvement for fear of being ridiculed by others and hence slow uptake of behaviours and services that require a male counterpart’s involvement.

The level of education for the VHTs might interfere with their ability to provide appropriate counselling for behavioural change as well as with the data collection. This is because the counselling is at times dependant on the information in the ANC card or child health card (CHC); VHTs who cannot read might not provide sufficient support to the household or register the necessary data. However, VHTs get an additional training to work with the ttC protocols, minimizing this risk. There might also be some recall bias during the end line survey, if the mothers did not manage to secure the relevant ANC and child health cards. However there is a plan to mitigate this by ensuring all pregnant women are given the cards during the first contact.

## 4. Discussion

The aim of this study is to evaluate the effect of ttC on pregnancy outcomes and newborn survival in rural Uganda with a hypothesis that ttC has no effect on pregnancy outcome and newborn survival. The backbone for this intervention is formed by the VHTs whose role it is to encourage positive behaviours for appropriate pregnancy and newborn care through community mobilization at the household level.

Pregnancy and delivery are generally considered events that do not require any medical care in most of the communities in Uganda [32]. This is due to cultural beliefs coupled with inadequate knowledge and poor household practices around maternal and newborn health care [33]. A lack of behavioral change communication to influence attitude change at the household level leads to poor and untimely pregnancy period care, with inadequate goal-oriented ANC attendance. This threatens newborn birthing practices, inadequate male partner involvement in pregnancy and newborn care, leading to poor pregnancy outcomes and newborn survival within the first 28 days of life.

Community mobilization for behavioral change such as the use of VHTs to implement ttC can be used to stimulate demand and utilisation of maternal and newborn services. In the project area, VHTs have been identified as a vehicle that can be used across the country to mobilize communities. If the VHTs are trained and equipped to implement ttC and are further supported to make timely household visits, it is hypothesized that this will affect behavioural change and therefore uptake of MNH services. ttC refers to a VHT approach of extending primary health care counselling to the household level, built around evidence-based, cost-effective key interventions for pregnant women and children under two. It is a package of key MNCH messages and actions that are disseminated and passed on to pregnant and breastfeeding mothers to bring about sustainable behavioural change at specific timelines. The strategy also targets key decision makers and those who influence decisions in households during home visits.

The study results will help in providing evidence and support programming focused on community-based support for uptake of MNCH services and influence behavioural change at the household level, through implementation of ttC. It is anticipated that if the VHTs target the mothers with key timely messages and support for positive feeding and caring practices during organized home visits, the following successes will be achieved: practices around goal-oriented ANC, essential newborn care, immediate postnatal care, and appropriate outcomes from pregnancy.

## Figures and Tables

**Figure 1 mps-03-00073-f001:**
[figure not shown]
Conceptual framework. MNH—maternal and newborn health, ANC—antenatal care, ttC—timed and targeted counselling.

**Figure 2 mps-03-00073-f002:**
[figure not shown]
CONSORT flow diagram.

**Figure 3 mps-03-00073-f003:**
[figure not shown]
The sampling flow framework.

**Table 1 mps-03-00073-t001:** Timed and targeted counselling (ttC) visits by village health teams (VHTs) to mothers during pregnancy or after childbirth.

Visit	Timing	Services Delivered by the VHTs
1	Before or at 3 months	Focuses on suspected pregnant mothers registered as ttC candidates. They are counselled on how to care for themselves during pregnancy, a list of danger signs during pregnancy is explained, and the family is encouraged to notify the VHT in the case of any of these danger signs. Families are counselled on what to do during pregnancy and when giving birth. Women pregnant for less than three months are advised to start antenatal care at three months.
2	At 4 months of pregnancy	This is to affirm that the pregnant mother went for ANC. The pregnant women are encouraged to go for the second ANC visit. Pregnant women are educated on the advantages of exclusive breastfeeding of children until 6 months of age and continuous breastfeeding until they reach the age of 2. Advantages of giving birth in a health facility and hand washing will be highlighted during this visit.
3	At 6 months of pregnancy	Discuss the birth plan, timing and place of the birth, exploring potential challenges faced by expectant mothers in reaching the health facility and ways of overcoming these challenges. Expectant mothers are given information on the different family planning methods and where to go for services, and are encouraged to utilize one of the methods after delivery.
4	8 months of pregnancy	The mother is educated about the early signs of true labor, danger signs during labor will be explained to the households, as well as appropriate action to take in the case of these danger signs. The mother is also encouraged to deliver at a health facility and have some emergency money available. This is also the visit at which the mother needs to have a clean birthing kit available (the “Mama Kit” [23]).
5–7	The newborn period	This visit is done three times in the first week after birth, on Days 1, 3 and 7. The VHT ensures that exclusive breastfeeding and essential maternal and newborn care are not only understood but also practiced. Mothers are educated on the need to seek health care if the neonate develops fever and/or a cough, and the need to go for routine growth monitoring and immunization.
8	When the baby is one month and 2 weeks	Malaria prevention is discussed here, as well as other illnesses, danger signs in the baby and immunization for the baby and hygiene practices. The VHT checks whether the child’s growth card has been plotted, gives support for exclusive breastfeeding, checks if the child has had its HIV confirmatory test as part of the prevention of mother-to-child transition of HIV program and whether the mother has any ideas about family planning methods.

**Table 2 mps-03-00073-t002:** Visits by VHTs to mothers during pregnancy or after childbirth in the control district as part of regular care.

Visit	Timing	Services Delivered by the VHTs
ANC	Pregnancy period	Ensuring that mothers actually attend ANC as early as required to acquire the initial goal-oriented services. Making the four visits to the household with a pregnant woman.
Newborn	Newborn (28 days)	Ensuring that the cord is healing, the baby is breastfeeding and that the initial immunization has been given to the child. Ensuring that the birth took place at the health facility and—if the birth happened at home—the VHT refers the mother and baby pair to the facility.
PNC	Postnatal period	Checking on the 6th hour that the health worker gives PNC. Visit the household around the 6th day and visit around 6 weeks after delivery to check whether the mother has plans of having the last PNC visit.
Immunization	Up to 9 months after birth	Conduct household mobilization visits to check on the completeness and preparedness for child immunization [26]. The Day 1 visit is for the VHT to check on the first day immunization. The VHT visits the household at around the 6th week after birth and then at around 10 weeks and 14 weeks after delivery.

**Table 3 mps-03-00073-t003:** Study period.

Study Period								
	Enrolment	Allocation	Post-Allocation					Close-Out
**TIMEPOINT**	Feb’19	Nov’19	Jan’20	Jun’20	Jan’21	Jun’21	Jan’22	Feb’22
Enrolment								
Eligibility screen	X	X	X	X	X			
Informed consent	X	X	X	X	X			X
Allocation		X	X	X	X	X		
Interventions								
[ttC implementation]			X	X	X	X	X	
[Control implementation]			X	X	X	X	X	
Assessments								
Baseline	X	X						
MTR Outcomes						X	X	
ETR Outcome								X

MTR outcome: Midterm review outcomes focusing on results from the ttC implementation alone. ETR outcome: End term review outcomes focusing on the comparison of ttC implementation and control intervention areas.

**Table 4 mps-03-00073-t004:** Study variables.

No	Variable	Description of Variable	Tool to Be Used
Dependent Variables			
1	Appropriate pregnancy weight gain at end of months pregnancy	Pregnancy weight gain of 11.5 kg to 16 kg by the end of the pregnancy	SQ
2	Newborn morbidity within the first 28 days of life	Newborn morbidity (focusing on cord infections, sepsis, asphyxia, fever, common flu and cold and diarrhea, pneumonia) within the first 28 days of life	SQ and ttCR
3	Appropriate birth weight	Appropriate birth weight of 2.5 kg or more	SQ
4	Mortality of newborns and mothers	If the mother died during pregnancy or childbirth, if the baby died either during pregnancy, childbirth or within the first 28 days of life.	SQ and ttCR
5	Overall maternal wellness	During pregnancy or newborn period, a mother does not develop sepsis, urinary tract infections, obstruction during birth or any danger signs during this period.	SQ and ttCR
Independent Variables			
1	Uptake of timely goal-oriented ANC	With a focus on the recommended four visits, the associated recommended services offered during these visits and timeliness of attendance.	VHTR, SQ and ttCR
2	Clean birthing practices	Birth attended by a skilled health provider, delivery happened in a health facility and a mama kit was used during the process.	SQ and ttCR
3	Essential newborn care practices (ENC) during the newborn period	Early initiation of breastfeeding, cord care practices, baby thermal care, sustained breastfeeding and baby WASH practices.	SQ and ttCR
4	Positive male involvement in pregnancy and newborn care	Man participates in at least one ANC, does an HIV test with the mother, available during birth, supports mother to help her rest, contributes finances for related logistics.	SQ

Notes: SQ: Study questionnaire, ttCR: ttC register, VHTR: Ugandan VHT household register.
